### Outcome measures

#### Primary outcome

The primary outcome is the first occurrence of a PPC within the first 14 postoperative hospital days. PPCs will be defined by the Melbourne Group Score (Table 3) which is reliable, valid [27, 28], sensitive to interventions [16], and has high inter-rater reliability [29]. It has eight clinical criteria: four factors relating to symptoms and four to diagnostic markers. A PPC will be diagnosed when four or more factors are present at any time from midnight to midnight on one postoperative day. The day a PPC is first diagnosed is the day of onset for purposes of time-to-event analysis.

**Table 3 Tab3:** PPC diagnostic criteria—Melbourne Group Score Version 3

When four or more of the following criteria^*^ are present anytime in the 24-h period 00:01 to 24:00 on a single postoperative day: 1. New abnormal breath sounds on auscultation different to preoperative assessment^+^ 2. Production of yellow, green, or brown sputum different to pre-morbid status^+^ 3. Pulse oximetry oxygen saturation (Sp0_2_) < 90% on room air or FiO2 on 0.21 on more than one consecutive postoperative day^**^ 4. Raised maximum tympanic temperature ≥ 38 °C on more than one consecutive postoperative day 5. Chest radiograph report of collapse/consolidation^# ***^ 6. Presence of infective organisms on sputum culture report^***^ 7. White cell count > 11 or < 3 8. Physician’s diagnosis of postoperative pulmonary complication (e.g. atelectasis, pneumonia, AECOPD, respiratory failure, upper respiratory tract infection) OR prescription of an antibiotic specific for respiratory infection	

*Abbreviations*: *PPC* postoperative pulmonary complications, *SpO2* pulse oximetry, *FiO2* fraction of inspired oxygen, *AECOPD* acute exacerbation of chronic obstructive pulmonary disease, *PEEP* positive end expiratory pressure, *CXR* chest X-ray

*If a blinded physiotherapist, nurse, or physician documents in the medical record the occurrence of a criterion, it can be taken as a positive finding. If no documentation present, a blinded assessor is required to assess this directly

^+^If no preoperative assessment or documentation assume normal at baseline

**For ventilated patients, if FiO_2_ ≥ 0.5 or PEEP ≥ 8, assume criterion 3 is present (do not alter FiO_2_), for all other patients set FiO_2_ to 0.21 and observe SpO_2_ for 2 min. If SpO_2_ drops below 90%, immediately reinstate previous FiO_2_. If not permissible to alter ventilation parameters, assume positive

^#^If no written report for a CXR is available and a patient has three other positive signs, a masked senior physiotherapist or ward medical officer is to be contacted to report verbally on the available CXR

***When there are no daily measures of CXR or sputum sampling, carry over a positive finding to the next consecutive postoperative day

Participants are assessed prospectively and daily for a PPC by a blinded assessor until the seventh postoperative day. From the 8th to the 14th postoperative day, additional PPC assessments are performed only as clinically suspected based on signs or symptoms of respiratory system deterioration reported within the medical record. To reduce the potential for missing data, retrospective collection of PPC data from the medical record will be permitted when a patient or assessor is unavailable for PPC assessment. Diagnostic components (chest X-ray (CXR), white cell count, sputum microbiology) are recorded only if results are available. All medical officers are masked to group allocation, and these diagnostic tests are ordered only as clinically indicated, and not routinely for the purposes of the ICEAGE trial.

For this trial, modifications have been made to reduce delays to possible diagnosis of a PPC (Table 3). An automatic positive threshold for the hypoxemia criterion has been set for ventilated patients; a positive CXR and/or sputum sample finding can be carried over to the next postoperative day if serial testing was not performed; a CXR can be verbally reported by a blinded senior respiratory physiotherapist or physician, rather than awaiting a radiologist report; and when three factors (out of a possible eight) are present, the blinded site investigator or ward physiotherapist will discuss the option of further diagnostic testing to confirm PPC with the participant’s treating physician. Additionally, patients with three out of eight criteria will be assessed twice daily for any clinical deterioration.

Any suspected PPC will be confirmed by a blinded senior physiotherapist, and the participant will then receive respiratory treatment as determined by the ward physiotherapist.

#### Secondary/exploratory trial outcomes

In hierarchical order:Referral by the surgical team or other allied health professional within the first 14 postoperative days for additional acute-ward physiotherapy rehabilitation, sub-acute hospital rehabilitation, or community-based rehabilitation. On receipt of a referral, or by the 14th postoperative day if referral not received, a blinded senior physiotherapist will review the participant’s current medical record and adjudicate for the requirement for rehabilitation services.Discharge destination from the acute hospital ward (home, rehabilitation facility, nursing home, or other hospital);Hospital LOS in days. This is defined as continuous days spent in any type of inpatient hospital service (i.e. acute care, sub-acute rehabilitation, or time at another hospital) from the day of admission for acute condition to the day of discharge to community. Hospital days will be sub-categorised into acute and sub-acute;Incidence of a prolonged postoperative ileus (PPOI) anytime from the fourth to the 14th postoperative hospital day. A PPOI is defined if two or more of the following criteria are met on or after the fourth postoperative day [30]: (i) nausea or vomiting, (ii) inability to tolerate an oral diet over last 24 h, (iii) absence of flatus over the last 24 h, (iv) abdominal distension, and (v) radiologic confirmation. The day which PPOI is first diagnosed is the day of PPOI onset for purposes of time-to-event analysis.Diagnosis of pneumonia defined as the presence of new CXR infiltrates along with at least two of the following: temperature > 38 °C, dyspnoea, cough, and purulent sputum, altered respiratory auscultation, and white cell count > 14,000/ml or leukopenia < 3000/ml on any day within the first 14 postoperative hospital days;Recovery of physical function and QOLi)Rate of change of the Modified Iowa Level of Assistance [31] (mILOA; Additional file 1) score over four measures taken second daily from the first postoperative day and a final score on the day of acute-ward discharge. The mILOA consists of four mobility tasks (supine to sitting on the edge of the bed, sit to stand, walking, and negotiation of one step), which are graded according to the level of assistance required, use of gait aid, and the distance that can be walked. Data will be extracted from the medical and physiotherapy records to score;ii)Rate of change in handgrip strength (kg) measured using a handheld dynamometer over four postoperative measures within the first 14 days. Measures will be taken at least 2 days apart;iii)Rate in change of the EuroQual QOL score [32] (EQ-5D; Additional file 2); measures to be taken directly from the patient over two consecutive measures separated by 48 h, within the first five postoperative days, and at 90 days following surgery;iv)Health-related QOL using World Health Organisation Disability Assessment Schedule V2 [33] (WHODAS; Additional file 3) change from self-rated status in the week prior to surgery, to day of discharge from acute care, and at 90 days following surgery;v)Physical capacity using Self-Assessment of Physical Activity Questionnaire [34] (SAQ; Additional file 4) from self-rated capacity regarding the week prior to surgery to 90 days following surgery;vi)Time in hours from end of operation to time able to achieve ambulation greater than 1 min;vii)Time in days from end of operation to achieve ambulation greater than 10 min;ICU LOS in days;Unplanned ICU admission during acute hospital stay;Mortality—in-hospital, 30 and 90days, and at 1 year;Sepsis within the first 7 days according to the Sequential Organ Failure Assessment (SOFA) for ICU patients and quick-SOFA for ward patients [35];Time in days to discharge from physiotherapy as determined daily using the Post-Operative Physiotherapy Discharge Scoring Tool [18] (Additional file 1);Time in days to readiness for hospital discharge within the first 14 postoperative days defined by standardised scoring criteria [36];Patient reported complications at 90 days using a standardised semi-structured interview [16];Hospital costs for the admission episode of care supplied by the participating centres’, or health departments’, costing data for each participant’s admission episode.

WHODAS, EQ-5D, and SAQ measures will be via direct interview whilst in hospital and by phone interview when patient at home. At 90-day (± 14 days) follow-up, if participant is unable to be contacted for a period of five consecutive working days, a standardised cover letter, questionnaires, and self-addressed return paid envelope will be posted. Forms not returned within 2 weeks will be considered lost to follow-up for post-discharge secondary outcomes. Figure 3 describes the schedule of events, trial conduct, and outcome measurements.

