## Methods/design

### Trial objectives

The primary objective of the Incidence of Complications following Emergency Abdominal surgery: Get Exercising (ICEAGE) trial is to estimate the effectiveness of physiotherapy on the incidence of PPC, including pneumonia, in patients following emergency open abdominal surgery.

Secondary objectives are to estimate the possible effect physiotherapy may have on prolonged postoperative ileus incidence, rates of referrals for formal sub-acute rehabilitation services, discharge destination, hospital length of stay (LOS) and costs, readiness to discharge from hospital, intensive care unit (ICU) LOS and readmissions, and rate of change to physical function and quality of life (QOL) whilst in hospital and at 90 days, and 1-year mortality.

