##### Early supervised ambulation—‘walk’

The standardised ambulation protocol [16, 17] (Table 2) will be provided as soon as practical after surgery by a physiotherapist. Patients will receive one supervised ambulation session per day until a threshold score is met [18] (Additional file 1), or discharge from hospital, whichever occurs first. At every session, the participant will be progressed sequentially through the protocol stages aiming to achieve a walking time of at least 10 min, but no more than 15 min, at an intensity of at least three on the Borg 10-point visual analogue scale (VAS) of perceived exertion [19], and where breathing is deeper than at rest. The treating physiotherapist will use a stopwatch to ensure the treatment session does not exceed 15 min and can provide a walking aid if clinically indicated. If necessary, ambulation sessions can comprise of equal work/rest intervals. Shorter, but not longer, rest times are allowable. The final achieved ambulation stage corresponds to total time walked, including the marching on the spot time, and not including rest periods.

**Table 2 Tab2:** ICEAGE ambulation protocol

Stage 1 (safety)	Sit over edge of bed/sit in chair minimum of 2 min
Stage 2 (safety)	March on spot 0–1 min
Stage 3 (ambulation)	March on spot/walk away from bedside 1–3 min
Stage 4 (ambulation)	March on spot/walk away from bedside 3–6 min
Stage 5 (ambulation)	Walk away from bedside 6–10 min
Stage 6 (ambulation)	Walk away from bedside 10–15 min
Stage 7 (ambulation)	Walk away from bedside > 15 min
Provide assisted early ambulation as soon as possible on the first postoperative day. At each session, progress through each stage in sequence. Time achieved in the session is accumulative. Aim to achieve rating of perceived exertion of greater than 3/10. Aim to assist patient to ambulate more than 10 min (stage 6 or greater). Once patient is able to ambulate past stage 3, patient can be assisted to ambulate with a physiotherapy assistant, as long as safe to do as determined by the ward physiotherapist. Interval training is permissible to obtain target walking time. Each interval of rest time must not exceed the preceding work time. Total session time is the accumulative work time. Provide assisted early ambulation once a day until discharged according to the discharge scoring tool.	

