Successful ambulation is defined as continuously marching on the spot beside the bed or walking away from the bedside for more than 1 min. Time from surgery to time of first successful ambulation will be recorded. If participants are unavailable or unable to achieve ambulation for more than 1 min, the assisted ambulation session will be attempted once again on the same day. The reasons for participants being unable to ambulate or not achieving a minimum of 10 min will be recorded. If a participant is unable to participate in upright ambulation, then no other non-ambulatory exercises will be provided that day. All treating therapists will be provided with protocol badge cards and trained by the site investigator. An allied health assistant can deliver the ambulation protocol once this is deemed safe to do so by the treating physiotherapist. The professional qualification of the person assisting each ambulation session will be documented.

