##### Supervised early rehabilitation—‘exercise more’

Intervention participants will receive physiotherapist supervised early rehabilitation lasting at least 30 min provided at least once daily. Rehabilitation will consist of a combination of ambulation and non-ambulatory chair- or bed-based exercises (Fig. 2) starting as soon as possible after surgery and continuing daily thereafter for at least the next five postoperative days or until at least five daily sessions are delivered. Exercises will be provided in a top-down hierarchical sequence starting from ambulation and aiming for the maximum physical activity type the participant is able to attempt. Exercise delivery progresses sequentially down the protocol until at least 30 min of activity have been accumulated. For example, participants will first be assisted to ambulate for at least 15 min with a goal to achieve at least 30 min. If time ambulated is less than 30 min, the participant will attempt resistive lower limb exercises in standing for the remaining time or until fatigue limits the performance. If time still remains less than 30 min, participants will attempt upper limb/lower limb resistance exercises in sitting until fatigued. This process continues until a minimum total treatment time of 30 min has been reached. A treating physiotherapist is also permitted to prescribe a personalised training activity based on a detected functional deficit to be incorporated within the rehabilitation programme. These targeted and individualised sessions will be recorded.

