All sessions will be conducted by a physiotherapist until at least the fifth postoperative day unless the supervising physiotherapist is confident that a therapy assistant or the participant will undertake the rehabilitation programme exactly as prescribed for the minimum 30 min. After the fifth postoperative day, daily treatment with a physiotherapist or therapy assistant will continue until either a referral for sub-acute rehabilitation services is made (see endpoints), a participant is discharged from hospital, or once a threshold score is met [18] (Additional file 1), whichever occurs first. If the patient meets the discharge score prior to the fifth postoperative day, daily treatment will continue until the fifth postoperative day but cease thereafter.

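### The first-ranked secondary outcome counts referral for extra acute-ward physiotherapy, which goes beyond the stated objective and overlaps the randomised treatment, so it can partly track allocation

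*Protocol article*

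**What the plan says.** In the protocol article, under Secondary/exploratory trial outcomes, the list opens: "In hierarchical order:Referral by the surgical team or other allied health professional within the first 14 postoperative days". The referral may be "for additional acute-ward physiotherapy rehabilitation, sub-acute hospital rehabilitation, or community-based rehabilitation". When a referral arrives, or by day 14 if none has, a blinded senior physiotherapist reviews the medical record to "adjudicate for the requirement for rehabilitation services".

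Trial objectives gives a narrower target: "rates of referrals for formal sub-acute rehabilitation services". The abstract's list of secondary outcomes and the Protocol endpoints section also mention sub-acute services only.

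The amount of ward physiotherapy differs by arm:

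- **Control** (Early supervised ambulation): one session a day until a threshold score is met, "aiming to achieve a walking time of at least 10 min, but no more than 15 min". In addition, "If a participant is unable to participate in upright ambulation, then no other non-ambulatory exercises will be provided that day".
- **Intervention** (Supervised early rehabilitation): "physiotherapist supervised early rehabilitation lasting at least 30 min provided at least once daily", with chair or bed exercise making up any shortfall in walking, for at least five days or sessions. "If the patient meets the discharge score prior to the fifth postoperative day, daily treatment will continue until the fifth postoperative day".

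Under Blinding, only the recruiting and treating physiotherapists know the allocation. Doctors, surgeons, nurses and discharge coordinators do not, and the record carries a standard phrase in place of treatment details.

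**The concern.** Two things are wrong with the outcome as defined.

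First, it is wider than the objective it serves. A reader of the objective or abstract would expect sub-acute referral. The definition adds a request for more physiotherapy on the acute ward.

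Second, the added component is the same kind of care as the randomised contrast. A request for additional ward physiotherapy is made relative to what the patient is already getting, and the protocol sets that amount by arm. Two equally recovered patients could therefore generate different referrals, because one is visibly receiving a short walk (or nothing on a non-walking day) and the other at least half an hour of exercise.

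At stake is how the first-ranked secondary outcome is interpreted. A lower rate in the intervention arm could be reported as less need for rehabilitation when part of it reflects the care allocated.

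**Working it through.** **Comparing the sections**

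| Place in the protocol article | Rehabilitation named |
|---|---|
| Abstract, secondary outcomes | sub-acute |
| Trial objectives | formal sub-acute |
| Protocol endpoints (event ending the exercise protocol) | sub-acute |
| Secondary/exploratory trial outcomes, first item | acute-ward, sub-acute hospital, or community |

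Community-based rehabilitation can be read as a form of sub-acute service. Acute-ward physiotherapy cannot. The mismatch therefore lies in that one component.

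**Who can refer.** The definition admits the surgical team, who are blinded, and other allied health professionals. It does not exclude the treating physiotherapist, who is not blinded. Blinded ward staff do not know the arm, but nothing in the text prevents them from noticing whether a patient is still being exercised.

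**Size.** The document gives no figure for this outcome, so there is none to reproduce. The only figure borrowed is the 131 per arm in the Sample size section, which does reproduce. For 20% v 8%, two-sided alpha 0.05 and 80% power:

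n = [1.96 × √(2 × 0.14 × 0.86) + 0.8416 × √(0.16 + 0.0736)]² / 0.12² = (0.9618 + 0.4068)² / 0.0144 = 130.1, rounded up to 131.

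Assumptions for the illustration, none of them from the document:

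- r = referral for sub-acute or community rehabilitation, equal in both arms (no effect on recovery): 10%, 20%, 30%
- a = acute-ward-only referral in control: 5%, 10%, 15%
- f = share of those acute-ward-only referrals that do not occur in the intervention arm because the care is already being given (displacement)

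Control rate pC = r + a. Intervention rate pT = r + a(1 − f). Risk ratio = pT / pC.

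Chance of a significant result favouring the intervention = 1 − Φ[(1.96 × SE0 − d) / SE1], where d = pC − pT, SE0 = √(2p̄(1 − p̄)/131), p̄ is the mean of the two rates, and SE1 = √([pC(1 − pC) + pT(1 − pT)]/131).

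Example with r = 20%, a = 10%, f = 0.5: pC = 0.30, pT = 0.25, risk ratio 0.83. SE0 = 0.0552, SE1 = 0.0551, and (1.96 × 0.0552 − 0.05) / 0.0551 = 1.06, so the chance is about 14.6%.

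Results at f = 0.5 (risk ratio; chance of a spurious significant benefit):

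| r | a = 5% | a = 10% | a = 15% |
|---|---|---|---|
| 10% | 0.83; 8.5% | 0.75; 18.5% | 0.70; 31.6% |
| 20% | 0.90; 6.9% | 0.83; 14.6% | 0.79; 25.7% |
| 30% | 0.93; 6.3% | 0.875; 13.0% | 0.83; 23.3% |

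At f = 0 every cell is 1.00 with a chance of 2.5%. At f = 1, the extreme case, the risk ratio runs from 0.40 to 0.86 and the chance from 14% to 90%. With the acute-ward component removed, the risk ratio under no effect is 1.00 whatever f is.

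**The case against.** A reader might infer that the outcome must favour the intervention even if recovery is the same, because control patients are denied what intervention patients already have. The document does not support that reading.

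- Control patients do receive daily supervised ward physiotherapy until the threshold score is met. A failed walking session is tried again the same day. They can be referred like anyone else, and intervention patients can also be referred for more.
- The surgical team is blinded and the record hides the treatment given. If referrers respond only to the patient's function, equal recovery gives equal referral.
- Requirement is adjudicated blind for every participant, so an extra referral is not simply counted.
- If less physiotherapy leaves a patient in greater need, that is a treatment effect the trial is meant to estimate.
- The difference in stopping rule ends at day 5, while the outcome runs to day 14. A control patient who has met the threshold score is an unlikely candidate for referral.
- Only one of three components is affected. Discharge destination, ranked second, and the split of hospital days into acute and sub-acute offer a partial check.

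Most of this stands, and it reduces the claim from a certain bias to a possible one. It does not remove it. The unblinded treating physiotherapist is not excluded as a referrer, and blinding to the arm is not blinding to care visibly given or absent. Adjudication does not fully close the gap either. A masked record does not let the adjudicator tell a shortfall in care from slow recovery. For patients discharged before day 14, the Blinding section allows treatment details into the record at discharge, which may precede adjudication. The mismatch with the objective is untouched by any of these arguments.

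**Conclusion.** The point holds in two parts. The definition of the first-ranked secondary outcome is wider than the objective, the abstract and the protocol endpoints; this is plain from the text and needs no assumption. The added acute-ward component overlaps the randomised treatment, so it can favour the intervention without any difference in recovery. That second part depends on referrers, possibly including the treating physiotherapist, reacting to the amount of ward physiotherapy being given.

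The size is unknown. On the assumed rates, the null risk ratio lies between 1.00 (no displacement) and about 0.70-0.93 (half displaced), with a 6-32% chance of a spurious significant benefit in the latter case against 2.5% in the former. These figures show that modest displacement would matter; they do not estimate what will happen. The outcome is secondary and the primary analysis is unaffected, so the change is advisable but not critical.

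**What to change.** Before unblinding, define the outcome as referral, or adjudicated requirement, for sub-acute inpatient or community-based rehabilitation, and state that the objective's sub-acute services include community-based services. Record the referral type for each participant. Report referral for additional acute-ward physiotherapy separately, by arm, as a descriptive measure of care rather than of recovery. Document the change with its date, since recruitment began in June 2015.

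The cost is a somewhat smaller event count. The article does not say that referral type is recorded, so this must be confirmed, or the type extracted from the medical record for participants already enrolled. Treatment, eligibility and sample size do not change.

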### Trial design

ICEAGE is a pragmatic, multicentre, parallel-group, randomised controlled trial. It is patient and assessor blinded, and powered for superiority. Eligible patients will be randomly assigned via concealed allocation into one of two physiotherapy treatment arms (Table 1). The control group will receive standard care physiotherapy from the first postoperative day consisting of education on prevention of complications with upright positioning, ambulation, and breathing exercises; a single deep breathing and coughing (DB&C) coaching session; and no more than 15 min of supervised ambulation once daily until a threshold score is met to discharge from this service. The intervention group will receive an enhanced physiotherapy care package from the first postoperative day consisting of (i) education on prevention of complications with upright positioning, ambulation, and breathing exercises; (ii) at least twice daily coached DB&C for the first two postoperative days; and (iii) at least 30 min of supervised early rehabilitation daily for the first five postoperative days. The mode of ambulation and respiratory physiotherapy will be standardised for both groups. The difference between groups will be (1) additional reminders and education as necessary for performance of independent exercises, (2) longer duration of ambulation and/or provision of individualised rehabilitation exercises, and (3) increased number of coached DB&C sessions (see Fig. 1 for the ICEAGE trial CONSORT diagram).

**Table 1 Tab1:** TIDieR descriptions of ICEAGE interventions

TIDieR criterion	Control	Intervention
Item 1. Brief name: provide the name or a phrase that describes the intervention	Standard care: ‘talk, walk, breathe’	Enhanced physiotherapy care: ‘talk more, exercise more, breathe more’

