### Eligibility and exclusion criteria

Local investigators will screen daily surgery lists and recruit eligible patients from the ICU and wards at participating hospitals. Eligible patients will be adults over 18 years having open emergency abdominal surgery. This is defined as time-critical surgery (within 48 h of decision to operate) for a condition that is an immediate or intermediate threat to life or organ survival, involving at least one incision greater than, or equal to, 5 cm anywhere in the abdomen and through the fascia, for an existing hospital patient or a person admitted through the emergency department and requiring at least an overnight stay. Exclusion criteria are as follows: procedures solely involving inguinal hernia repairs, appendectomies, organ transplantation, thoracic, or gynaecological surgery; a PPC diagnosis anytime in the 24 h prior to eligibility screening; a pre-existing condition where the patient is unable to stand upright and ambulate for 1 min without a seated rest; severe cognitive impairment; unable to understand spoken English without the assistance of an interpreter (as determined by the research assistant, site investigator or ward physiotherapist performing eligibility screening); within 7 days of elective abdominal surgery; planned repeat surgery within 5 days of emergency procedure; approaching imminent death or withdrawal of medical treatment within 48 h of their surgical procedure; medical orders not to participate in early active rehabilitation; patients unable to be randomised by the research team within 48 h of surgery; enrolment in another clinical trial with similar endpoints; and previous enrolment in ICEAGE.

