##### Secondary outcomes

Binomial outcomes including rehabilitation referrals, pneumonia, PPOI, unplanned ICU admissions, patient-reported complications, and mortality will be analysed using multivariate robust random effects Poisson generalised linear regression.Time-to-event binomial outcomes (e.g. PPC, pneumonia, PPOI, achievement of ambulation goals of 1 and 10 min; and hospital and ICU LOS; and mortality) will be compared by estimating hazard ratios using Cox proportional hazards regression, with and without covariate adjustment where necessary and graphically illustrated using Kaplan-Meier methods.Measures involving estimation of rate of change over time (QOL and functional capacity) will be analysed using repeated-measures mixed effects linear regression or ordered logistic regression for rank-ordered scale measures.Hospital costs will be compared using mixed effects linear regression. Log transformation of highly skewed cost data will be performed. Depending on the adequacy of the data for purposes of economic analysis, a cost-utility may be conducted.

All outcomes will be analysed on an intention-to-treat basis. An intention-to-protocol sensitivity analysis will be performed by identifying as a separate group participants who received more than 80% of planned protocol sessions as per group allocation. Other planned sensitivity analyses will be made according to age (> 65), surgery type (colorectal, upper gastrointestinal, other), preoperative self-reported physical capacity, and gender. Sensitivity of outcome estimates to missing data will be evaluated using multiple imputations. All analyses will be performed using Stata MP2 V14 (StataCorp, College Station, TX, USA).

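### Hospital length of stay is counted from admission, so preoperative days that neither arm can change attenuate the planned hazard ratio and cost some precision

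*Protocol article*

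**What the plan says.** In the protocol article, Secondary/exploratory trial outcomes defines hospital length of stay as "continuous days spent in any type of inpatient hospital service", running "from the day of admission for acute condition to the day of discharge to community". The only subdivision is this: "Hospital days will be sub-categorised into acute and sub-acute". No split separates days before surgery from days after it.

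Eligibility and exclusion criteria admits surgery "for an existing hospital patient or a person admitted through the emergency department". The operation must be "time-critical surgery (within 48 h of decision to operate"; that limit runs from the decision, not from admission. The same section excludes "patients unable to be randomised by the research team within 48 h of surgery", so randomisation follows the operation. Trial design then starts treatment after surgery: "The control group will receive standard care physiotherapy from the first postoperative day", with the same starting day for the enhanced package.

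Under Statistical methods, Secondary outcomes lists length of stay among the time-to-event outcomes: "and hospital and ICU LOS; and mortality) will be compared by estimating hazard ratios using Cox proportional hazards regression".

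**The concern.** Every preoperative day in the count lies before randomisation, and neither arm can alter it. On a clock that starts at admission, the Cox model compares patients who share a hospital day but not a stage of recovery. On hospital day 10, a patient with 1 preoperative day is 10 - 1 = 9 days past surgery, while one with 8 preoperative days is 10 - 8 = 2 days past it. Mixing the two in one risk set blurs the contrast between arms.

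Hospital stay is a named secondary objective and third in the hierarchical list of secondary outcomes. At stake is how sensitively that question is answered: an HR closer to 1, and a lower chance of detecting a real shortening. The article's other clocks already start later. The ambulation outcomes run from the end of the operation, and the Cox analysis of pulmonary complications runs from the end of surgery or anaesthesia.

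**Working it through.** **The plan's own figure.** The article gives no sample size, power, mean or SD for length of stay. Its only power statement concerns pulmonary complications, 20% v 8%, two-sided alpha 0.05, power 80%. With the pooled-variance formula:

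n per arm = [1.960 × √(2 × 0.14 × 0.86) + 0.842 × √(0.20 × 0.80 + 0.08 × 0.92)]² / 0.12² = (0.962 + 0.407)² / 0.0144 ≈ 130.1, rounded up to 131, or 262 in total.

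This matches the article. It says nothing about length of stay, but it supplies the 131 per arm used below.

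**Order of events.** Admission, then the decision to operate, then surgery within 48 h of that decision, then randomisation within 48 h of surgery. Treatment is from the first postoperative day. Time from admission to surgery is therefore always before allocation, and the article sets no upper limit on it.

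**Effect on the difference in mean days.** Write stay as P + T, with P preoperative days (independent of arm) and T postoperative days. The difference in means is E[T, control] - E[T, intervention], because P cancels. The variance becomes Var(T) + Var(P), so

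SE(admission)² = SE(surgery)² + 2 × Var(P)/131.

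- P equally likely 0, 1 or 2: Var(P) = 0.667; √(0.75² + 0.010) = 0.76 days.
- P exponential, mean 2: Var(P) = 4; √(0.76² + 0.061) = 0.80 days.
- 20% with mean 8 (exponential), the rest 0-2: mean 0.2 × 8 + 0.8 × 1 = 2.4; Var(P) = 0.2 × 128 + 0.8 × 1.667 - 2.4² = 21.2; √(0.75² + 0.323) = 0.94 days.

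Simulation gave the same standard errors, with a mean difference of about 2.0 days on either clock.

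**Effect on the planned HR (simulated, 131 per arm).** All inputs on stay are assumptions. Two models for postoperative stay were used, each without deaths or censoring:

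- Weibull: shape 1.5, control mean 10 days, true HR 1.4, 400 trials per setting.
- Log-normal: median 10 days, log SD 0.6, intervention stay multiplied by 0.8, 1,500 trials per setting. The exponential preoperative draws are rounded down, so their realised means are 1/(e^(1/m) - 1) = 1.5, 2.5 and 3.5 days for m = 2, 3 and 4.

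| Postoperative model | Preoperative days | HR, from surgery | HR, from admission | Power, from surgery | Power, from admission |
|---|---|---|---|---|---|
| Weibull | 0-2 | 1.40 | 1.39 | 76% | 77% |
| Log-normal | 0-2 | 1.405 | 1.400 | 76% | 75% |
| Weibull | exponential, mean 2 | 1.40 | 1.38 | 75% | 71% |
| Log-normal | exponential, mean 2 | 1.41 | 1.39 | 79% | 73% |
| Log-normal | exponential, mean 3 | 1.40 | 1.35 | 76% | 67% |
| Log-normal | exponential, mean 4 | 1.40 | 1.33 | 76% | 64% |
| Weibull | 20% mean 8, rest 0-2 | 1.38 | 1.30 | 73% | 51% |

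With 400 trials the Monte Carlo error of a power near 75% is √(0.75 × 0.25/400) ≈ 2 percentage points, so 76% v 77% is no difference. For the same kind of mixture as in the last row (20% averaging 8 days), the log-normal model gave power of 62% on the admission clock. With a true HR of 1.3 in the Weibull model, that mixture moved the HR from 1.31 to 1.24 and power from 55% to 42%.

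**No treatment effect.** With exponential preoperative stay of mean 3 days, the HR is 1.00 and the type I error 5.1% on both clocks.

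**The case against.** Several points on the other side are sound.

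- **Validity.** A reader might infer immortal-time bias, because nobody enrolled could be discharged before surgery and yet that time counts in the Cox model. The documents do not support this. The preoperative days are fixed before allocation, so they balance in expectation, and the simulation without effect shows correct type I error. The cost is sensitivity, not false positives.
- **Scope.** A reader might also infer that any effect on stay is diluted. That holds for the HR and for relative measures. The difference in mean days is unbiased and only noisier.
- **Length of the preoperative stay.** Weeks of prior stay should not be assumed because inpatients are eligible. The clock starts at admission for the acute condition, which can be read as leaving out an earlier unrelated stay. Patients within 7 days of elective abdominal surgery are excluded. In a population needing time-critical surgery, 0 to 2 days is plausible for most, and the loss is then near zero.
- **Choice of measure.** Admission to discharge is total bed use, which suits a pragmatic trial and matches the cost outcome for the admission episode. The outcome list also has time to readiness for discharge within a 14-day postoperative window, although that does not replace length of stay.

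What remains is that the preoperative days are in the tested outcome, nothing in the article removes them, and the planned summary is an HR.

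**Conclusion.** The point holds as a modest loss of efficiency in one secondary outcome. Starting at admission attenuates the Cox HR and widens its uncertainty. Its size cannot be established from the article, which gives neither preoperative stay nor an expected effect on stay. Under the assumptions above it ranges from negligible (0-2 days) through modest (exponential mean 2-4 days) to material. The material case needs a sizeable minority with long preoperative stays, which the article neither shows nor rules out. Even there the result depends on the postoperative model (power 51% or 62%). The primary analysis of pulmonary complications is untouched.

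**What to change.** Define the tested outcome as days from surgery to discharge to the community, and count the acute and sub-acute split from the same day. Report admission-to-discharge stay descriptively and use it for costing.

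The change is one line of outcome wording. No new data should be needed: the section on early supervised ambulation already records time from surgery to first successful ambulation, so the time of surgery is captured. Up to 48 h between surgery and randomisation would stay in the count, but this is bounded. The cost is that the tested figure no longer equals total bed use.
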